### Intervention Description

This will be a longitudinal cohort study with 2 groups: the *intervention group*, which will receive the CH technology package at home, and the *usual care* group, which will not have any CH technology package at all. Selection to the CH or usual care group will be made by the PwD and their informal caregiver; thus, we will have adopter (intervention) and nonadopter (usual care) groups. The volunteer PwD-caregiver dyads will freely choose in which group they would like to participate as we acknowledge that this is a vulnerable population at an advanced age who might not be technology educated or might not feel comfortable with technology.

The CH technology package (Multimedia Appendix 2) consists of an online health platform designed for the informal caregiver that runs in a tablet computer (Samsung Galaxy Tab A 10.1, 2016) connected to a range of PwD monitoring devices for home use, including a BP monitor (Omron M6), an electronic weighing scale (Withings), and an activity and sleeping tracker (Withings Go). The online platform includes 4 sections (Multimedia Appendix 3). The first (Multimedia Appendix 4) consists of an information and resource section that provides access to website links and videos from Irish dementia experts with reputable information regarding dementia management and helpful advice about daily home care. The second section (Multimedia Appendix 5) provides daily and weekly questionnaires that gather health-related information about the PwD, that is, mood, nutrition, activity, bowel movements, and medication compliance, which are completed by the caregiver and viewed by the health care professionals involved in the PwD’s care. In addition, questionnaires for the informal caregivers are included to assess their own health and well-being, that is, mood, energy levels, sleeping quality, and anxiety levels. This will be used for research purposes only and not viewable for health care professionals. The third section (Multimedia Appendix 6) includes a journal to be used as an online diary where the informal caregivers can maintain recordings of events, and it also contains summary reports of changes in the PwD care plan provided by the health care professionals from previous consultations. The fourth section (Multimedia Appendix 7) offers a dashboard for the caregivers and health care professionals to view the PwD activity levels, sleep patterns, BP, and weight, recorded by the monitoring devices provided along with the health platform. During the deployment, the informal caregiver has access to the health platform at any time using the tablet computer. They will have to measure the PwD’s BP once a week and input the results into the *measurements* section. Safety range values of each individual BP will be set up in the health platform during the first assessment, so this measurement will act as their reference BP value. If BP measurements fall outside these parameters (2 points above or below the first assessment values), a message will pop up on the tablet screen advising the informal caregivers to check how the PwD is feeling at that moment and to take another BP measurement in 30 min. Following this, if the value measured is still outside the normal limits and the PwD is feeling unwell, they will be advised to contact their general practitioner. Weight has to be measured by the informal caregiver once a month and will be automatically uploaded from the scale to the health platform via Wi-Fi. Daily activity and sleeping, tracked from the activity wrist tracker, is automatically uploaded via Bluetooth into the health platform. In addition, the informal caregivers will be prompted through messages under each section name to complete the daily and weekly questionnaires on the platform, to take the weight and BP, and to have a look at the information section, which will be updated with new resources regularly.

The encrypted online platform will securely connect all the key stakeholders involved in the PwD’s care (ie, informal caregiver, general practitioner, public health nurse, and hospital geriatric services). As mentioned above, the generated data will be presented in the platform and made available for the informal caregivers and the health care professionals as an objective measure of the patient’s health status.

### Outcomes Measurements

A multidimensional profile of the well-being of caregivers and PwDs will be tracked longitudinally over the duration of the study, with some brief measures recorded daily (questionnaires and PwD’s activity and sleeping), another weekly (BP) or monthly (weight), and others at quarterly intervals (assessments questionnaires). These measures will be contrasted between the intervention and usual care groups at discrete time points and over time. The daily and weekly monitoring will consist of simple Likert-type questions about the PwD and caregiver (completed by the caregiver) along with the physical activity of the PwD measured in steps and sleep duration.

More detailed outcomes will be compared and evaluated through international validated questionnaires administered by the researcher and that are commonly used in the clinic to measure well-being. Choosing the appropriate questionnaires and the right time for completing them was decided after a concise literature review that also required meetings and advice from experts in dementia and considerations of the demands on the caregiver and PwD. Our outcome domains can be divided into 2 groups that are described below (Multimedia Appendix 8). In addition, qualitative interviews will take place at months 3 and 9 of the year of deployment to analyze caregivers’ satisfaction with the CH platform along with the usability and user experience.

#### Person With Dementia–Related Outcomes

The cognitive status level in the PwD will be measured using the *Mini-Mental State Examination* (MMSE) questionnaire. It is composed of 11 questions that cover 5 areas of cognitive function: orientation, registration, attention and calculation, recall, and language. The maximum score is 30, with a score of 23 or less being indicative of cognitive impairment. This is a quick and easy tool to administer directly to the PwD and is very useful when having to conduct it repetitively [19,20].

Behavioral and neuropsychiatric symptoms will be assessed with the short version of the *Neuropsychiatric Inventory Questionnaire* (NPI-Q). It is a way of providing a brief assessment of the PwD’s neuropsychiatric symptoms, which has been seen to be sensitive and reliable to capture changes in time related to delusions, hallucinations, agitation or aggression, depression or dysphoria, anxiety, elation or euphoria, apathy or indifference, disinhibition, irritability or lability, aberrant motor behavior, sleep and night-time behavior disorders, and appetite and eating disorders. It is based on responses of the caregivers who must also rate these symptoms in terms of frequency (how frequent those symptoms occur), severity (how severe and how much it affects the PwD), and distress (how distressing is it for them as caregivers and how much it may affect them). The NPI-Q does not have a cutoff score and, therefore, does not have a numeric scoring. Each domain is scored for frequency, severity, and associated caregiver distress, and the interviewer has to analyze them in those given terms [21-23].

Quality of life will be measured with the *Dementia Quality of Life* (DEMQOL) questionnaire, to gain an insight into their health-related quality of life. This is designed to work across dementia subtypes and care arrangements and is suitable for all the stages of the disease. It is composed of 2 questionnaires: (1) DEMQOL, a 28-item questionnaire answered by the PwD (self-reported quality of life) and (2) DEMQOL-Proxy, a 31-item questionnaire answered by the caregiver (PwDs’ caregiver- reported quality of life). Scored items are summed to produce a total score, with higher scores meaning a better health-related quality of life [24,25].

Anxiety and depression levels will be examined using the *Hospital Anxiety and Depression Scale* (HADS), a simple and brief self-reported questionnaire. A total summary score classifies the respondent into 3 groups, depending on their levels of depression and anxiety, into normal, borderline case, or abnormal. This questionnaire does not provide a diagnosis as it was created for screening purposes only [26,27].

PwD functional levels will be assessed with the *Disability Assessment for Dementia* questionnaire, designed for community-based individuals with Alzheimer dementia type, but it has been used in other types of dementia research more recently. It is a tool used by health care professionals to investigate the PwD levels of dependency and to guide the provision of tailored interventions for PwD. In addition, as a research tool, it can be used to describe the functional characteristics of the PwD and the progression of the disease. A total score is converted out of 100, with the result of a percentage that gives an understanding of the PwD global function in ADLs. Higher scores mean less disability in conducting ADLs, with lower scores indicating more dysfunction and more dependency on the caregiver [28].

PwD frailty will be examined with the *Survey of Health, Ageing, and Retirement in Europe Frailty Instrument (SHARE-FI)*. It is a 5-item validated scale created by Romero-Ortuno et al [29,30], which predicts frailty and mortality in primary care similarly to a frailty index based on a comprehensive geriatric assessment. It is quick and easy to administer as it only requires 5 simple measurements to be entered in an open-access online calculator, which we have incorporated into our health platform.

PwDs’ risk of falls; gait, and mobility assessment will be conducted with *Kinesis Quantitative Timed Up and Go (QTUG*). It is an online app tool for the QTUG test, validated through research by the company *Kinesis* that measures different phases of the *Timed Up and Go* test [31]; time in turning; and reflects overall locomotor task ability, variability, and stability. QTUG can identify a large range of temporal gait parameters. Using an internal algorithm integrates these with clinical falls risk indicators to calculate a falls risk score [32,33].

#### Caregiver-Related Outcomes

Quality of life in the caregiver will be measured using the EuroQol-5 dimention-5 level instrument (*EQ-5D-5L*) [34]. It is a standardized measure of health status, creating a simple descriptive profile and a single index value that can be used for the clinical and economic evaluation of health status and health care. It consists of 2 parts. The first part is the descriptive system that comprises 5 dimensions, mobility, self-care, usual activities, pain/discomfort, and anxiety/depression, each of these having 5 possible response options: no problems, slight problems, moderate problems, severe problems, and extreme problems. The interviewee must choose 1 answer that best represents their health state. The second part is the visual analogue scale (EuroQol group Visual Analogue Scale, EQ-VAS), which is a 20-cm vertical scale scoring from 0 to 100, with endpoints marked with “the best health you can imagine” for the 100 score and “the worst health you can imagine” for the 0 score. The interviewee has to mark out a point in the scale, providing a score representing their self-rated score. From the first part, an individual health state is defined for each respondent combining 1 level from each of the 5 dimensions, giving a personalized digit code for their health status. The second part, the EQ-VAS, provides a quantitative measure of the interviewed health status.

Anxiety and depression levels will be assessed using the same tool as applied for the PwD, the HADS, which is described above.

The burden of care and ability to cope will be estimated using the *Zarit Burden Interview questionnaire*. It is composed of 22 questions about the impact of the PwD’s disabilities in the caregiver’s life and has been designed to reveal the stress experienced by the caregiver. For each item, the caregivers must indicate how burdened they are (never, rarely, sometimes, quite frequently, or nearly always). A total score can be calculated from the summing of each answer, with higher scores indicating higher levels of burden and stress because of the caring process [35,36].

Caregiver sleep quality will be examined with the *Pittsburgh Sleep Quality Index*, designed to evaluate the overall sleep quality for 1 month. It is a 19-item self-reported questionnaire with 7 subcategories: subjective sleep quality, sleep latency, sleep duration, habitual sleep efficiency, sleep disturbances, use of sleeping medication, and daytime dysfunction. This questionnaire was initially created to measure the sleeping quality in psychiatric populations but has been widely used for clinical and research purposes [37,38].

Caregivers’ satisfaction with the platform and usability of the system will be investigated via semistructured individual interviews conducted before and after the technology deployment, with the support of a previously designed interview guide that includes the following topics: (1) reason for participating in the project; (2) platform feedback on usability, usefulness, helpfulness, expectations, suitability, and improvements; (3) caregivers’ impressions of PwD perceptions of the CHESS platform; and (4) caregivers’ perceptions of home care technology in general. The interviews will be audio recorded for later transcription and analysis.

### Timing of Measurements

In both groups, PwD-caregiver dyads will be followed up for 12 months during which they will continue with their traditional care plan, but in addition, the intervention group will receive the CH package for their use at home during 6 months (months 3 to 9 of the yearly follow-up), thus enabling a baseline phase, intervention phase, and a postintervention phase to be delineated. During the initial assessment (month 0), PwDs’ past medical history and PwDs’ and informal caregivers’ social history and demographic data will be obtained. Further comprehensive assessments related to the caregivers’ and PwDs’ emotional and physical well-being will be performed at the initial assessment and at 3, 6, 9, and 12 months using the international and standardized validated questionnaires explained above. They will be completed electronically on the researchers’ administrators interface of the health platform by the caregiver and the patient, with the help of the researchers (see Table 1 for the comprehensive list of questionnaires and their timing during the 12 months follow-up, and see Multimedia Appendix 8 for a screenshot of the administrators’ interface view of the questionnaires). Respondent burden is a key consideration, and so in this way, all in-depth questionnaires are reserved for quarterly face-to-face interviews with the researchers, whereas daily and weekly questionnaires modules with which the caregiver interacts independently through the user interface are kept short and simple.

**Table 1 table1:** Quarterly assessments and timing with the caregiver and person with dementia during the yearly follow-up.

Participant	Month 0	Month 3	Month 6	Month 9	Month 12
PwD^a^	Past medical history, vital signs; DEMQOL^b^, HADS^c^, MMSE^d^, QTUG^e^; Frailty (SHARE-FI^f^), DAD^g^, DEMQOL, proxy, NPI-Q^h^	DEMQOL, HADS, MMSE, QTUG, Frailty (SHARE-FI), DAD, DEMQOL proxy	DEMQOL, HADS, MMSE, QTUG, Frailty (SHARE-FI), DAD, DEMQOL proxy, NPI-Q	DEMQOL, HADS, MMSE, QTUG, Frailty (SHARE-FI), DAD, DEMQOL proxy	DEMQOL, HADS, MMSE, QTUG, Frailty (SHARE-FI), DAD, DEMQOL proxy, NPI-Q
Caregiver	EQ-5D-5L^i^, HADS, IPAQ^j^, NVS^k^, PSQI^l^, ZBI^m^	EQ-5D-5L, HADS, NVS, PSQI, ZBI	EQ-5D-5L, HADS, IPAQ, NVS, PSQI, ZBI	EQ-5D-5L, HADS, NVS, PSQI, ZBI	EQ-5D-5L, HADS, IPAQ, NVS, PSQI, ZBI

^a^PwD: person with dementia.

^b^DEMQOL: Dementia Quality of Life.

^c^HADS: Hospital Anxiety and Depression Scale.

^d^MMSE: Mini-Mental State Examination

^e^QTUG: Quantitative Timed Up and Go.

^f^SHARE-FI: Survey of Health, Ageing, and Retirement in Europe Frailty Instrument.

^g^DAD: Disability Assessment for Dementia.

^h^NPI-Q: Neuropsychiatric Inventory Questionnaire.

^i^EQ-5D-5L:EuroQol group-5 dimension- 5 level questionnaire.

^j^IPAQ: International Physical Activity Questionnaire.

^k^NVS: Newest Vital Signs.

^l^PSQI: Pittsburgh Sleep Quality Index.

^m^ZBI: Zarit Burden Interview.

### Initial Users’ Evaluation

A first model of the CH platform was developed over 12 months. Once the first stage of development of the platform was completed, we decided to conduct various levels of user testing with researchers and clinicians from our group to detect any possible platform failures or bugs, to verify that it worked according to our expectations, and to redefine the user interface based on their findings. During February 2017, 5 researchers and clinicians used the technology for 1 week, completing the tasks as the caregiver would and, also, wearing the activity tracker 24/7 as the PwD would. They were encouraged to think and to use the platform as a caregiver would and were provided with a list of the tasks to be completed during the week, that is, to measure their weight and to measure their BP at least once, to have a look at the information section (to watch some videos and to access some of the websites’ links provided), to write down minimum 1 entry in the journal, and to have a daily look at their activity and sleeping, so as to ensure that the devices were accurately syncing and being presented accurately in the measurements section. A log was created specifically for them to record any potential issues that appeared during the platform and device use, with the idea of solving them before the deployment phase. The platform seemed to work according to our scheme, and devices were syncing appropriately. Data were showed in the measurements section, and videos and links from the resources section were working properly. Researchers feedback was used to make some small changes in the platform’s look to give it a clearer and cleaner aspect and make it easier to use.

### Data Analysis

Quantitative data from the participants’ quarterly assessments and daily monitoring data will be exported from the platform in the form of Excel documents. Descriptive statistics will be used to summarize the initial demographic data from our sample, which are obtained from the medical notes and the initial assessment examination (month 0), and for describing the findings of the questionnaires at each assessment point (months 3-12). Exploratory factor analysis will be conducted on the measured variables to identify the main constructs in our sample and how they correlate and interact with each other.

The main data collection points will be at 2 stages: months 0 and 12, as they will give us insight into the progress of the disease and the quality of life of the PwD and caregivers over 1 year, whereas interim data points will be available at 3, 6, and 9 months. Thus, the primary analysis of these repeated measures within each individual will be assessed using linear mixed models (LMMs). LMMs are suitable for correlated data such as these, and random intercepts and slopes can be allowed for individuals and subgroups. Change over time will be assessed, and differences between subgroups and interactions between covariates will be explored.

We also want to investigate changes in the scores between each assessment point (at 0, 3 6, 9, and 12 months). For this, analysis of variance or the equivalent nonparametric tests will be used. Regarding the assessments at months 3 to 9, these are the months when the technology is deployed at their homes and in which we can assess any potential impact derived from its use between the intervention and the usual care groups. This group comparison will be estimated by comparing the change in the volunteers’ scores between those 2 assessments (month 3 and month 9) using *t* tests or the correspondent nonparametric tests when appropriate.

For this, a sample size calculation was derived using a rule of thumb for 20 observations for each dependent variable, so a sample size of 60 PwD-caregiver dyads is proposed. For the comparison of outcomes between the intervention and the usual care groups, caregiver burden and quality of life will be the primary outcome measure assessed at enrollment and at 6 and 12 months. Acknowledging that the PwD can deteriorate over time with a decline in their cognitive and functional status, we will use scores adjusted for baseline patient dependence and neuropsychiatric symptoms (analysis of covariance, ANCOVA model). We hypothesis a moderate between-groups effect size (*d*=0.5), so with 80% power and alpha=.05, a sample of 64 individuals in the intervention group and 64 in the usual care group is required for the *t* test. Adjusting for ANCOVA by sqrt (1-p2), where the p is the conservative correlation of 0.5 between repeated measures [39], results in a sample of 55 in each group. To account for dropout, 60 PwD-caregiver dyads will need to be recruited for each group. SPSS software (IBM Corp Version 24.0) will be used for this statistical analysis.

Analysis of the qualitative data obtained from the transcribed individual semistructured interviews will be analyzed using content analysis [40]. A guiding codebook will be used for this analysis, which will be created based on the topics examined in the interviews outlined above. The emerged categories will be organized, analyzed, and compared for generating themes. NVivo software version 12 for Macintosh (QSR International) will be used to organize the thematic analysis.

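### The sample-size paragraph gives both 60 dyads and 60 dyads per group and does not say which governs recruitment or which analysis each serves

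*Protocol article*

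**What the plan says.** Both figures stand in the sample-size paragraph of Methods, Data Analysis.

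- The paragraph opens by referring back to the analyses above it and invokes a "rule of thumb for 20 observations for each dependent variable, so a sample size of 60 PwD-caregiver dyads is proposed". It does not say how many dependent variables are counted, which ones they are, or how the 60 dyads divide between groups.
- It then names caregiver burden and quality of life as primary for the comparison of intervention with usual care, to be analysed by ANCOVA, and gives a power calculation. At d = 0.5, "with 80% power and alpha=.05", "a sample of 64 individuals in the intervention group and 64 in the usual care group is required" for a t test. The next step is "Adjusting for ANCOVA by sqrt (1-p2), where the p is the conservative correlation of 0.5 between repeated measures", which gives 55 per group.
- It concludes: "To account for dropout, 60 PwD-caregiver dyads will need to be recruited for each group". That is 2 × 60 = 120 dyads. No dropout rate is stated.

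The text immediately before this paragraph describes a different group comparison: change from month 3 to month 9, the period when the technology is in the home, by an unadjusted t test or its nonparametric equivalent.

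**The concern.** The study enrols one cohort and needs one recruitment target. The two figures differ by a factor of two, and the paragraph does not reconcile them. The 60-dyad sentence follows directly on the month 3 to 9 group comparison, so on a plain reading both figures are offered for comparing intervention with usual care. A rule of so many observations per variable says nothing about the power of a two-group test.

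A team that stopped at 60 dyads could point to one sentence of the plan in support, yet the comparison of the groups would fall well short of the 80% power that the same paragraph states. A null result would then be hard to interpret.

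**Working it through.** **Inputs.** From the sample-size paragraph: d = 0.5, power 80%, alpha .05, correlation ρ = 0.5, and the figures 64, 55 and 60 per group. Two-sided testing is not stated but is inferred: two-sided reproduces 64, while one-sided gives 50 to 51. The even split of 60 dyads into 30 and 30 is an assumption.

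**1. Reproducing the stated figures**

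- Unadjusted t test: n = 2(1.960 + 0.842)² / 0.5² = 62.8, so 63 per group by the normal approximation. The noncentral t gives 63.77, so 64, as stated.
- ANCOVA step as the article applies it: 64 × √(1 − 0.5²) = 64 × 0.866 = 55.4, so 55, as stated.
- Dropout: 1 − 55/60 = 8.3%, the rate implied by going from 55 to 60.

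The power calculation therefore leads to 60 per group. It gives no support to 60 overall.

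**2. The rule of thumb**

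60 / 20 = 3, so the rule gives 60 if three dependent variables are counted with one observation per dyad. The article does not name three.

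**3. Power if 60 dyads is the total, 30 per group**

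The noncentrality is d* × √(n/2), with n = 30 and √15 = 3.873.

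- Unadjusted t test on change. At ρ = 0.5 the SD of a change is √(2(1 − 0.5)) = 1 times the raw SD, so d* = 0.5. Noncentrality 1.94, power **47.8%**.
- ANCOVA with the article's own factor on n: d* = 0.5 / √0.866 = 0.537. Noncentrality 2.08, power **53.4%**.
- ANCOVA with the standard variance factor 1 − ρ² = 0.75: d* = 0.5 / √0.75 = 0.577. Noncentrality 2.24, power **59.4%**.

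**4. Same methods at other sizes (two-sided, noncentral t)**

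| Dyads per group | t test on change | ANCOVA, article's factor | ANCOVA, 1 − ρ² |
|---|---|---|---|
| 30 / 30 | 47.8% | 53.4% | 59.4% |
| 27.5 / 27.5 (60 total less 8.3%) | 44.5% | 49.9% | 55.6% |
| 20 / 40 (uneven self-selection) | 43.5% | 48.8% | 54.5% |
| 60 / 60 | 77.5% | 83.1% | 88.0% |
| 55 / 55 (120 total less 8.3%) | 73.8% | 79.7% | 85.1% |

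**5. Detectable difference at 80% power with 30 per group**

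- t test: d = 0.736.
- ANCOVA, article's factor: 0.736 × √0.866 = 0.685.
- ANCOVA, standard factor: 0.637.

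**The case against.** The best defence is that only the later sentence uses the language of recruitment, while the 60-dyad figure is merely proposed. A careful team would recruit 60 per group, and one that stopped at 60 would contradict an explicit statement. It can be added that the two figures may have been meant for different analyses, or that the 60 was meant per group throughout. Any of these may be what was intended, but the text says none of them, so the contradiction stands. What does stand of the defence is that the chain from 64 to 55 to 60 per group is not miscalculated. The defect is a failure to reconcile two figures.

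Several stronger readings are tempting and go beyond the text:

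- **That 60 dyads gives under 50% power, without qualification.** With 30 per group this holds for the unadjusted t test. The ANCOVA that the article names for its primary outcomes has 53% to 59% before dropout. It reaches about 50% or slightly below only after the implied dropout or an uneven split, and only with the article's own factor.
- **That the rule of thumb fails on its own terms.** Table 1 lists 8 questionnaires and tests for the person with dementia and 6 for the caregiver, and 14 × 20 = 280. But the article does not say which entries count as dependent variables. The rule also counts observations, not dyads: with five assessments per dyad, 60 dyads could supply up to 300 observations on an instrument given at every visit. Failure of the rule cannot be asserted.
- **That the 60 was sized for the exploratory factor analysis.** The factor analysis is described earlier in the section, before the mixed models and the group tests. Nothing links it to the rule.
- **That 60 per group settles everything.** It supports the ANCOVA. For the month 3 to 9 t test it gives 77.5% before dropout, and the article itself asks for 64 per group for an unadjusted t test.

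**Conclusion.** The concern holds as an unreconciled contradiction: one paragraph gives 60 dyads and 120 dyads, without stating which governs recruitment or for which analysis. If 60 is the total and splits evenly, power before dropout is about 48% for the t test on change and about 53% to 59% for the ANCOVA, against the stated 80%.

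These figures assume two-sided testing at .05, d = 0.5, and the article's correlation of 0.5 taken at face value. That 60 is a total is the natural reading, but the article does not use those words. An even split is not assured, because dyads choose their group; a 20/40 split would lower power further. On every two-sided reading examined, 60 dyads in total falls far short of 80%.

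**What to change.** 1. Delete the rule-of-thumb sentence as a basis for the group comparison. State one recruitment target, 60 dyads per group (120 in total), and tie it to the ANCOVA of the primary outcomes.
2. For the month 3 to 9 comparison, either state that the unadjusted t test has about 77.5% power at 60 per group before dropout (about 73.8% at 55), or analyse it with adjustment for the month 3 score.
3. If only about 60 dyads in total will be recruited, replace the 80% claim with the power or the detectable difference for that number: on an even split before dropout, roughly 48% for the t test and 53% to 59% for the ANCOVA, or d of about 0.74 and 0.64 to 0.69.

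The cost is wording only. The downside is a less favourable power statement, for the month 3 to 9 t test in any case and for the whole group comparison if the total stays near 60.

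### The visits named for the primary group comparison (enrolment, month 6, month 12) omit the start and end of the month 3 to 9 deployment, and the plan does not say which group contrast is primary

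*Protocol article*

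**What the plan says.** All sections are in the Protocol article.

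- **Exposure.** Under Timing of Measurements, "the intervention group will receive the CH package for their use at home during 6 months (months 3 to 9 of the yearly follow-up"). The section gives the purpose as "thus enabling a baseline phase, intervention phase, and a postintervention phase to be delineated".
- **When impact is assessable.** Data Analysis describes months 3 to 9 as the deployment months, "in which we can assess any potential impact derived from its use between the intervention and the usual care groups". It plans a group comparison of the change in "scores between those 2 assessments (month 3 and month 9"), by t test or a nonparametric equivalent.
- **Analysis called primary.** The same section states that "The main data collection points will be at 2 stages: months 0 and 12", and that "the primary analysis of these repeated measures within each individual will be assessed using linear mixed models (LMMs").
- **Primary outcomes.** The sample-size paragraph of Data Analysis, introducing the comparison between intervention and usual care, says "caregiver burden and quality of life will be the primary outcome measure assessed at enrollment and at 6 and 12 months". The ANCOVA and the calculation giving 64, then 55, then 60 per group follow.
- **Data available.** Table 1 lists the Zarit Burden Interview (ZBI) and EQ-5D-5L at months 0, 3, 6, 9 and 12, and Timing of Measurements applies the follow-up to both groups.

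**The concern.** The design sets out three phases so that the effect of the package can be read across the middle one. The sentence that fixes the primary outcomes then uses one visit from each phase, and none of the three marks either boundary of the deployment. Two things are at stake.

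First, the primary comparison may understate an effect that is present while the package is in use. Dyads choose their own group (Intervention Description). With an enrolment baseline, any divergence between adopters and non-adopters during the three months before deployment therefore enters the estimated effect.

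Second, the analysis called primary, the visits attached to the primary outcomes and the comparison matched to the exposure are described separately and never ranked. A reader of the final report could not tell which result was meant to carry the conclusion, and a favourable one could be picked afterwards.

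**Working it through.** **1. The plan's own sample size.** Inputs from Data Analysis: d=0.5, 80% power, alpha 0.05 (taken as two-sided), correlation 0.5.

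- t test: 2 × (1.960 + 0.842)² / 0.5² = 62.8, so 63 by normal approximation. The noncentral t solution is 63.77, so 64, as stated. A one-sided test would give 50, so the two-sided reading is the right one.
- ANCOVA with the plan's multiplier: 64 × √(1 − 0.5²) = 55.4, so 55, as stated.
- Dropout: 1 − 55/60 = 8.3%, giving 60 per group.

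The figures reproduce, so the issue is timing, not arithmetic. The usual ANCOVA factor for n is 1 − r², giving 64 × 0.75 = 48. That is a separate matter, but it explains why 55 per group gives more than 80% power below.

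**2. Visits set against exposure (months 3 to 9).**

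| Visit | Exposure received | Named for primary outcomes | ZBI and EQ-5D-5L in Table 1 |
|---|---|---|---|
| Month 0 | 0 of 6 months; deployment starts 3 months later | yes | yes |
| Month 3 | 0 of 6; deployment starts | no | yes |
| Month 6 | 3 of 6 | yes | yes |
| Month 9 | 6 of 6; deployment ends | no | yes |
| Month 12 | 6 of 6, ended 3 months earlier | yes | yes |

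Reading month 3 as pre-deployment fits the interviews, which are placed at months 3 and 9 under Outcomes Measurements and described as before and after deployment under Caregiver-Related Outcomes. If the intended quality-of-life measure were DEMQOL rather than EQ-5D-5L, the table would be the same, because DEMQOL is also taken at all five visits.

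**3. Illustration of dilution.** The article gives no time course for the effect. Assume d=0.5 at month 9 and let a fraction f of it be present at the visit analysed. With baseline adjustment at r=0.5, the effective d is 0.5f / √0.75. With 55 per group the noncentrality is that value × √(55/2) = that value × 5.244.

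| f | d at visit | Effective d | Noncentrality | ANCOVA power | Unadjusted t-test power |
|---|---|---|---|---|---|
| 1 | 0.500 | 0.577 | 3.03 | 85% | 74% |
| 0.75 | 0.375 | 0.433 | 2.27 | 61% | 50% |
| 0.5 | 0.250 | 0.289 | 1.51 | 32% | 26% |
| 0.25 | 0.125 | 0.144 | 0.76 | 12% | 10% |

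The same table serves month 6 and month 12. A steady build-up from month 3 to month 9 would put month 6 at f=0.5. An effect that has levelled off by month 6 would put it at f=1, with no loss. At month 12, f depends on how much persists after removal.

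**4. Moving the contrast.** With d=0.5 and r=0.5 kept, a month 9 comparison adjusted for month 3 gives the same 64 and 55. No extra dyads are needed.

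**The case against.** The strongest reply is that the exposure-window comparison is already in the plan, that month 6 lies inside the deployment, and that month 0 is a legitimate unexposed baseline. All of that is true. A reader might infer that the plan ignores the deployment period or cannot detect an effect; it does neither. What stands is that the planned month 3 to 9 test is not designated primary, and the visits that are attached to the primary outcomes are different ones.

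Month 12 is also defensible as a target. The article expects gains in knowledge and autonomy, which could outlast the package, and it justifies months 0 and 12 by disease progress and quality of life over the year. That supports keeping month 12, but it does not settle which contrast is primary.

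Four stronger readings are tempting, and the article does not support them:

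- **The month 3 to 9 test is sized only by the rule of thumb.** The words introducing that rule have no clear referent. The formal calculation is stated for a t test, and the only group comparison by t test that the article names is the month 3 to 9 one.
- **The mixed model forces a straight line through an on/off exposure.** The article allows random intercepts and slopes but does not say how the fixed effect of time is coded.
- **The study has 32% or 12% power.** The plan attaches d=0.5 to its own comparison. The losses arise only if the effect peaks at month 9 and is smaller at the other visits.
- **NPI-Q and IPAQ must be added at months 3 and 9.** Neither is a primary outcome, NPI-Q is available at month 0 as the baseline adjuster, and the article treats respondent burden as a key consideration.

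**Conclusion.** The point holds as an inconsistency within Data Analysis, and between it and Timing of Measurements. The visits named for the primary outcomes miss both ends of the exposure, and no single group contrast is identified as primary.

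The mismatch in dates follows directly from the text and needs no assumption. The cost in power does need one. Over the range examined, ANCOVA power runs from 85% (no dilution) to 12% (a quarter of the effect present), given d=0.5 at month 9, r=0.5 and 55 per group. These figures show sensitivity to timing and do not predict the study's power. The plan's sample-size figures are not in question here.

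A month 3 baseline would keep drift before deployment out of the estimate. It would not remove drift between self-selected groups after month 3.

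**What to change.** Reconcile the statements in Data Analysis by naming one primary contrast for ZBI and EQ-5D-5L: the intervention versus usual care difference at month 9, adjusted for the month 3 score. The planned linear mixed model can supply it, with time as a categorical factor and a group-by-time term. Then:

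- make month 6 (mid-exposure) and month 12 (persistence after removal) secondary;
- report the month 0 to month 3 change by group as a pre-deployment check on the self-selected groups;
- reword the sentences that give months 0 and 12, and enrolment, 6 and 12 months, as the main or primary points;
- keep the month 0 NPI-Q as the adjuster for neuropsychiatric symptoms, since it is not taken at month 3.

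The cost is wording. Both measures are already scheduled at months 3 and 9 in both groups, and the sample size is unchanged at the plan's own d and correlation. Because the study is already running, the change should be dated and recorded before any comparison of the groups is seen. The downside is that the longer-term persistence comparison becomes secondary.
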